#### Height and weight

Weight was measured in light clothing without shoes using a portable digital scale (Model no. UC-321PC, A&D Company Ltd, Tokyo Japan) to the nearest 0.1 kg. Height was recorded to the nearest 0.1 cm using a portable stadiometer (Model no. PE087, Mentone Educational Centre, Australia). Body mass index (BMI) was calculated using the equation (weight[kg]/height[m]^2^) and BMI-z scores were calculated using the 'LMS' method [37].

#### Body fat

Percentage body fat, fat mass (FM) and fat free mass (FFM) were determined using the Imp(tm) SFB7 bioelectrical impedance analyzer, which is a multi-frequency, tetra polar bioelectrical impedance spectroscopy device [38].

#### Muscular fitness

A modified version of the 90° push-up test (90PU) was used as a measure of upper body muscular endurance [39]. Participants started in the push-up position with their hands and knees touching the floor and the arms at shoulder width apart. Keeping their back straight and hips extended, participants then lowered themselves to the ground until there was a 90-degree angle at the elbows, with upper arms parallel to the floor. A tester held their hand at the point of the 90-degree angle so that the shoulder of the participant touched the observer's hand, then pushed back up. The push-ups were completed in time to a metronome set at 40 beats per minute with one complete push-up every three seconds. The prone support test was used to provide a measure of core abdominal isometric muscular endurance. Participants started lying face down on a gym mat, then propped themselves up on their elbows and toes so that their body was in a straight line (hips and knees are not to be flexed). The participant was timed to see how long they could hold the prone support position before dropping a knee to the ground.

#### Physical activity

Actigraph accelerometers (MTI models 7164, GT1M and GT3X) were worn by participants during waking hours for seven consecutive days, except while bathing and swimming. The accelerometers were worn on a small elastic belt and positioned in front of the right hip. Trained RAs, following standardized accelerometer protocols [40] fitted the monitors and explained the monitoring procedures to study participants. To improve compliance with the study protocols, participants were sent text messages each morning during the seven-day monitoring period to remind wear. Data were collected and stored in 30-second epochs and the mean activity counts per minute (CPM) was calculated. Age and gender specific cut-points were used to categorize PA into sedentary, light, moderate and vigorous intensity activity [41].

#### Dietary behavior

Dietary intake was assessed using the Australian Eating Survey (AES). AES is a 135-item semi-quantitative food-frequency questionnaire (FFQ) which was previously tested for reliability and relative validity [42]. The tool demonstrated acceptable accuracy for ranking nutrient intakes in Australian youth 9 to 16 years [43] and is currently being validated in adults. Portion sizes for individual food items were accessed from the Australian Bureau of Statistics (ABS) and unpublished data from the 1995 Australian National Nutrition Survey or the "natural" serving size for common items such as a slice of bread. Subjects were asked about frequency of their consumption over the previous 6 months. The frequency options ranged from 'Never' to '4 or more times per day' but varied depending on the food item.

Twenty-one questions relate directly to the intake of vegetables and 11 to fruit, with seasonal availability of some fruits considered in the nutrient analysis. The frequency categories were listed as for other food items, with the question, "When the following fruit is in season, how often do you usually eat it?" with seasonal availability determined by data provided by fresh food markets in Sydney, NSW, in addition to referring to supermarket literature that indicated the months of the year different seasonal fruit was available. The AES includes additional questions about the total number of daily serves of fruit, vegetables, bread, dairy products, eggs, fat spreads, sweetened beverages and snack foods, as well as asking the type of bread, dairy products and fat spreads used. Twelve questions relate to food-related behaviors, including items on frequency of take-away food consumption and eating while watching television.

#### Sedentary behaviors

The Adolescent Sedentary Activity Questionnaire (ASAQ) was used to provide a self-report of time spent in sedentary behaviors [44]. The ASAQ requires respondents to report time spent in the following activities: watching television/videos/DVDs, computers, e-games and e-communication, study, reading, sitting with friends, telephone use, listening or playing music, motorized travel, hobbies and crafts, all performed out of school hours.

#### Physical activity and dietary social-cognitive mediators

Social cognitive scales for PA (Table 3) and dietary (Table 4) behaviors based on constructs from SCT [45] were designed for the study. Participants completed separate PA and nutrition scales for the following constructs: self-efficacy, social support, environmental perceptions (situation), behavioral strategies (self-control), outcome expectations (perceived benefits), outcome expectancies (value placed on benefits) and intentions. The validity and two week test-retest reliability of the measures was assessed in a sample (N = 171) of Australian adolescents (66 = males; 105 = females; mean age = 13.6 ± 1.2 years). Selected subscales (i.e., strength, body fat, appearance, general physical self-concept and global self-esteem) from Marsh's Physical Self-Description Questionnaire [46] were included as potential outcomes and mediators of PA behavior.

**Table 3 T3:** Physical activity mediator scales

Variables	Description and example items	Range (No. of items)	ICC (95% CI)	α	χ^2^	*df*	*p*	GFI	RMSEA
*Physical activity mediators*									
Self-efficacy	Confidence in ability to adopt, maintain and overcome barriers to PA behaviors. For example: *"I can still find the time to be physically active even when I've had a busy day"*.	1-6 (5)	0.91 (0.88 to 0.93)	0.69	3.82	5	0.58	0.99	0.00
Environmental perceptions	An individual's mental representation of their environment that may influence their PA behavior:								
	• Home environment - For example: *"At home I have access to equipment that helps me to be physically active - e.g. bikes, balls, skateboards"*.	1-6 (3)	0.88 (0.83 to 0.91)	0.63	11.22	8	0.19	0.98	0.05
	• School environment - For example: *"At school, facilities are available during recess/lunch for me to be physically active - e.g. the gym, dance studio, sports equipment".*	1-6 (3)	0.85 (0.79 to 0.89)	0.65	11.22	8	0.19	0.98	0.05
Social support	Social influences that reinforce PA through encouragement and role modeling:								
	• Peer support - *"...how often did you make plans with your friends to be physically active together?'*	1-5 (4)	0.91 (0.88 to 0.94)	0.78	27.40	19	0.10	0.97	0.05
	• Family support - For example: *"... how often did members of your family participate in physical activities/sports with you?"*	1-5 (4)	0.86 (0.81 to 0.90)	0.74	27.40	19	0.10	0.97	0.05
Behavioral strategies	Self-reinforcement for PA achieved through setting goals, monitoring behavior and self-reward. For example: *"...did you organize to be physically active with a friend or family member?"*	1-5 (6)	0.91 (0.88 to 0.93)	0.79	15.45	9	0.16	0.97	0.07
Outcome expectations	Anticipated outcomes of PA such as the benefits. For example: *"Participation in regular physical activity can help me to improve my fitness".*	1-6 (5)	0.82 (0.75 to 0.86)	0.75	11.26	5	0.03	0.97	0.09
Outcome expectancies	The value placed on anticipated outcomes of PA. For example: *"How important is improving your fitness to you?"*	1-4 (5)	0.88 (0.83 to 0.91)	0.66	15.74	5	0.01	0.97	0.11
Intentions	Intention to be physically active.	1-4 (1)	0.79 (0.72 to 0.85)	NR	NR	NR	NR	NR	NR

*Note*. *ICC *= Intra class correlation for 2-week test-retest reliability; α = Cronbach alpha; χ^2 ^= Chi-square; *df *= degrees of freedom; *p *= probability; GFI = goodness of fit index; RMSEA = root mean square of approximation; NR = Not relevant.

**Table 4 T4:** Dietary social-cognitive mediator scales

Variables	Description and example items	Range (No. of items)	ICC (95% CI)	α	χ^2^	*df*	*p*	GFI	RMSEA
*Dietary mediators*									
Self-efficacy	Confidence in ability to adopt, maintain and overcome barriers to healthy eating behaviors. For example: *"I find it easy to choose a healthy snack when I eat between meals - e.g. fruit, reduced fat yoghurt"*.	6	0.89 (0.85 to 0.92)	0.70	17.41	9	0.04	0.97	0.07
									
Environmental perceptions	An individual's mental representation of their environment that may influence their dietary behaviors. For example: *"At home, fruit is always available to eat - e.g. fresh, canned or dried".*	4	0.81 (0.75 to 0.86)	0.79	0.90	2	0.64	1.00	0.00
Social support	Social influences that reinforce healthy eating through encouragement and role modeling. For example: *"...how often do your parents prepare a healthy home-cooked dinner for you?"*	6	0.89 (0.85 to 0.92)	0.68	10.24	9	0.33	0.98	0.03
Behavioral strategies	Self-reinforcement for healthy eating achieved through setting goals, monitoring behavior and self-reward. For example: *"During meals do you leave food on your plate once you feel full?"*	6	0.88 (0.84 to 0.91)	0.75	6.69	9	0.67	0.99	0.00
Outcome expectations	Anticipated outcomes of healthy eating such as the benefits. For example: *"Healthy eating can help me to control my weight".*	5	0.84 (0.79 to 0.88)	0.72	14.67	5	0.01	0.97	0.10
Outcome expectancies	The value placed on anticipated outcomes of healthy eating. For example: *"How important is controlling your weight to you?"*	5	0.89 (0.87 to 0.92)	0.65	4.10	5	0.54	0.99	0.00
Intentions	Intention to eat healthily. For example: *"... do you intend to choose reduced-fat foods and drinks whenever you have a choice?"*	6	0.83 (0.77 to 0.87)	0.71	9.77	5	0.08	0.98	0.08

*Note*. PA = physical activity; ICC = Intra class correlation for 2-week test-retest reliability; α = Cronbach alpha from the study sample; χ^2 ^= Chi-square; *df *= degrees of freedom; *p *= probability; GFI = goodness of fit index; RMSEA = root mean square of approximation.

#### Process evaluation

A detailed process evaluation will be undertaken to assess the feasibility of the NEAT Girls program. This will include recruitment (achievement of target sample size), retention (retention rates at 12- and 24-month follow-ups), attendance (at enhanced school sport, interactive seminars and lunch-time physical activities), intervention fidelity (24 randomly selected sessions will be observed by a member of the research team and participants will submit their PA and nutrition handbooks), acceptability and program satisfaction (students and teachers will complete detailed process evaluation questionnaires at the completion of the study).

### Statistical methods

Statistical analyses will be conducted using mixed models which have the advantage of being robust to the biases of missing data and provide appropriate balance of Type 1 and Type 2 errors [47]. The models will be specified to adjust for the clustered nature of the data and the analysis conducted using established models [48]. The study was designed to randomize in matched pairs, matching has been shown to improve the power if the number of groups per condition is greater than 10 or the matching correlation is greater than 0.30. As this study has less than 10 groups the power analysis and analysis plan have conservatively been designed to incorporate the matching if the correlations between the matching variable and the dependent variable (BMI) or the correlation on BMI between members of a pair are high [49]. Multiple imputation will also be considered as a sensitivity analysis if the dropout rate is substantial. Cohen's *d *[50] will be used to determine effect sizes and will be calculated using the mean difference (12- and 24-months minus baseline) between groups and the pooled standard deviation of change for the whole group. Mediation analysis will be conducted by assessing hypothesized social-cognitive mediators of PA and nutrition behavior change using the PRODuct of Confidence Limits for INdirect effects (PRODCLIN) program [51]. The characteristics of the study participants at baseline are reported in the results section of this paper. Estimates of baseline characteristics for the treatment and control groups were adjusted for clustering by school using PROC MIXED in SAS V 9.1 (SAS Institute Inc, Cary, NC) and intraclass correlation coefficients (ICCs) were calculated for key outcomes. Differences between intervention and control groups at baseline were examined using independent samples t-tests in PASW Statistics 17 (SPSS Inc. Chicago, IL) software and alpha levels were set at *p *< .05.

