**Methods/Design:**

The Nutrition and Enjoyable Activity for Teen Girls (NEAT Girls) intervention will be evaluated using a group randomized controlled trial. NEAT Girls is a 12-month multi-component school-based intervention developed in reference to Social Cognitive Theory and includes enhanced school sport sessions, interactive seminars, nutrition workshops, lunch-time physical activity (PA) sessions, PA and nutrition handbooks, parent newsletters, pedometers for self-monitoring and text messaging for social support. The following variables were assessed at baseline and will be completed again at 12- and 24-months: adiposity, objectively measured PA, muscular fitness, time spent in sedentary behaviors, dietary intake, PA and nutrition social-cognitive mediators, physical self-perception and global self-esteem. Statistical analyses will follow intention-to-treat principles and hypothesized mediators of PA and nutrition behavior change will be explored.

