## Results

Twelve schools were recruited and 357 participants were assessed at baseline, representing a 99.2% of the targeted sample size (Table 5). Results are provided as means ± standard deviations, unless otherwise noted. There were no statistically significant differences between control and intervention groups at baseline for any of the demographic or outcome variables. Most participants were born in Australia (97.8%), spoke English at home (98.6%), and identified their cultural background as Australian (85.4%). A high percentage of participants were classified as overweight (26.1%) and obese (16.8%).

**Table 5 T5:** Baseline characteristics of study sample

Characteristics	Control (*n *= 179)		NEAT Girls (*n *= 178)		Total (*N *= 357)	
	Mean	SD(SE)	Mean	SD(SE)	Mean	SD(SE)

Age (years)	13.2(13.2)	.4(0.04)	13.2(13.2)	.4(0.04)	13.2	.5(0.024)

Country of birth, *n *(%)^1^	174	97.2%	175	98.3%	349	97.8%
Language spoken at home, *n *(%)^2^	176	98.3%	176	98.9%	352	98.6%
Cultural background^3^						
Australian, *n *(%)	153	85.5%	152	85.4%	305	85.4%
Asian, *n *(%)	1	.6%	3	1.7%	4	1.1%
European, *n *(%)	18	10.1%	18	10.1%	36	10.1%
Other, *n *(%)	7	4.0%	4	2.2%	11	3.1%

Weight (kg)	58.4(58.4)	13.8(1.44)	58.4(58.3)	14.2(1.44)	58.4	13.9(0.74)
Height (m)	1.61(1.61)	.07(0.00)	1.60(1.60)	.06(0.01)	1.60	.07(0.00)
BMI (kg/m^2^)	22.6(22.6)	4.5(0.48)	22.7(22.7)	4.7(0.48)	22.6	4.6(0.24)
BMI *z*-score	.78(0.78)	1.17(0.12)	.82(0.82)	1.12(0.12)	.80	1.14(0.06)
BMI Category						
Underweight, *n *(%)	1	.6%	1	.6%	2	.6%
Healthy weight, *n *(%)	99	55.3%	103	57.9%	202	56.6%
Overweight, *n *(%)	50	27.9%	43	24.2%	93	26.1%
Obese, *n *(%)	29	16.2%	31	17.4%	60	16.8%
BIA (body fat %)	28.3(28.3)	6.8(1.02)	29.6(29.5)	6.5(1.03)	28.9	6.7(0.35)

Push-up test (reps)	12(12.1)	8(1.12)	12(12.1)	9(1.12)	12	8(0.44)
Prone support test (s)	48(48.0)	34(5.32)	54(53.4)	34(5.33)	51	34(1.82)

MVPA (mins/day)^4^	33.6(33.7)	16.4(2.63)	36.9(36.6)	17.7(2.63)	35.3	17.1(1.27)
Meeting MVPA guideline, *n *(%)^5^	11	9.6%	13	11.2	24	10.4%

SSR (mins/day)	262.4(262.5)	170.5(18.81)	284(284.5)	162.3(18.90)	273.2	166.6(8.83)
Meeting SSR guidelines, *n *(%)^6^	23	12.8%	17	9.6%	40	11.2%

Dietary intake (kJ/kg/day)	163.4(163.3)	81.3(8.69)	173.0(173.8)	91.4(8.71)	168.2	86.5(4.58)

*Note*. SD = Standard deviation; SE = Standard error; BMI = Body mass index; BIA = Bioelectrical impedance analysis; MVPA = Moderate-to-vigorous physical activity minutes per day; s = Seconds; mins = Minutes; SSR = Small screen recreation.

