^1^Participants born in Australia

^2^Participants who speak English at home.

^3^One participant did not report their cultural background.

^4^n = 114 (Control), n = 116 (Intervention); N = 230 participants wore accelerometers for ≥600 minutes on ≥4 day.

^5^Participants meeting the MVPA of ≥60 minutes of MVPA.

^6^Participants not exceeding the SSR recommendations of ≥120 minutes each day.

The ICC values for BMI, BMI z-score, moderate-vigorous physical activity (MVPA) minutes, SSR and kilojoules per kilogram per day (kJ/kg/day) were .03, .03, .09, .04 and .03, respectively. Two hundred and thirty participants wore accelerometers for ≥600 minutes on at least four days. From this number, only 10.4% met the PA recommendations of at least 60 minutes of MVPA each day (averaged across days monitored). A small proportion of participants (11.2%) met the SSR guidelines of less than 2 hours/day and girls reported consuming 168 (± 87) kilojoules per kilogram per day.

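### Cohen's d is fixed as a raw change-score difference with no stated baseline adjustment, so the Table 5 gaps in several secondary outcomes carry into the reported effect sizes

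*Protocol article*

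**What the plan says.** The Statistical methods section assigns the analyses to mixed models, chosen as "mixed models which have the advantage of being robust to the biases of missing data". Of adjustment it says: "The models will be specified to adjust for the clustered nature of the data and the analysis conducted using established models". It does not say that the baseline value of the outcome is adjusted for. The sample size section mentions two covariates but does not name them.

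The size of an effect is to be expressed as Cohen's d, which "will be calculated using the mean difference (12- and 24-months minus baseline) between groups and the pooled standard deviation of change for the whole group". The rule is not limited to BMI.

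On baseline balance, the Results state: "There were no statistically significant differences between control and intervention groups at baseline for any of the demographic or outcome variables". For accelerometry, a footnote to Table 5 reports that "N = 230 participants wore accelerometers for ≥600 minutes on ≥4 day", out of 357 girls assessed. The abstract adds: "Statistical analyses will follow intention-to-treat principles".

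**The concern.** A difference in raw change subtracts the whole baseline gap between arms, although only part of that gap is expected to remain at follow-up. The rest appears in d as if it were an effect. For BMI this hardly matters, because BMI is balanced. For noisier secondary outcomes with visible gaps in Table 5, part of d is foreseeable before any follow-up data exist. A non-significant baseline test does not remove the gap.

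Two lesser costs follow. A change score is less precise than a baseline-adjusted difference. And if d is computed from each girl's own change, those without a valid baseline accelerometer record are left out of the MVPA effect size, although the mixed model was chosen for its handling of missing data. Effect sizes are what later readers and meta-analyses are likely to take from the paper.

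**Working it through.** **Inputs.** From Table 5 (NEAT Girls minus control), in parentheses the cluster-adjusted means: MVPA 33.6 (33.7) vs 36.9 (36.6) min/day; prone support 48 (48.0) vs 54 (53.4) s; body fat 28.3 (28.3) vs 29.6 (29.5) %; SSR 262.4 (262.5) vs 284 (284.5) min/day; BMI 22.6 vs 22.7; push-ups 12.1 vs 12.1 adjusted. Total-sample SDs: 17.1, 34, 6.7, 166.6 and 4.6 for the first five. The baseline to follow-up correlation ρ is not in the article; 0.3, 0.5 and 0.7 are assumed.

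**The article's own statement on balance.** Independent t-tests from the unadjusted figures give p = 0.14 for MVPA, 0.10 for prone support, 0.066 for body fat, 0.22 for SSR and 0.84 for BMI. For these outcomes the statement of no significant differences is reproduced.

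**Shift in d with no true effect.** With equal variances at both visits, and ρ applied to the whole gap:

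- expected raw-change difference = −(1 − ρ) × gap
- SD of change = SD × √(2(1 − ρ))
- shift in d = −(gap / SD) × √((1 − ρ)/2), where the root is 0.592, 0.500 and 0.387 at ρ = 0.3, 0.5 and 0.7

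| Outcome | Adjusted gap | Gap/SD | Raw-unit shift, ρ = 0.5 | d shift at ρ = 0.3 / 0.5 / 0.7 |
|---|---|---|---|---|
| MVPA | +2.9 min/day | 0.170 | −1.45 | −0.10 / −0.08 / −0.07 |
| Prone support | +5.4 s | 0.159 | −2.7 | −0.09 / −0.08 / −0.06 |
| Body fat | +1.2 points | 0.179 | −0.60 | −0.11 / −0.09 / −0.07 |
| SSR | +22.0 min/day | 0.132 | −11.0 | −0.08 / −0.07 / −0.05 |
| BMI | +0.1 kg/m² | 0.022 | −0.05 | −0.01 / −0.01 / −0.01 |
| Push-ups | 0 | 0 | 0 | 0 |

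With the unadjusted gaps (3.3, 6, 1.3 and 21.6) the four affected outcomes run from −0.05 (SSR, ρ = 0.7) to −0.12 (body fat, ρ = 0.3). A negative shift is unfavourable for MVPA and prone support and favourable for body fat and SSR.

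**How much of the gap is between schools.** Schools were randomised, so the individual-level ρ need not apply to the whole gap. The approximate individual-level share of the variance of an arm mean, against the squared cluster-adjusted SE for control in Table 5, is:

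- MVPA (ICC .09): 17.1² × 0.91 / 115 = 2.3, against 2.63² = 6.9, about one third
- body fat: at most 6.7² / 179 = 0.25, against 1.02² = 1.04, about 24%
- prone support: at most 34² / 179 = 6.5, against 5.32² = 28.3, about 23%

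If the school part persisted fully and the gap split in these proportions, the body fat shift at ρ = 0.5 would be 0.5 × 0.24 × 1.2 = 0.14 points rather than 0.60, and the MVPA shift about 0.5 × (1/3) × 2.9 = 0.48 min/day rather than 1.45.

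**Precision.** Adjusted variance over change-score variance = (1 − ρ²) / (2(1 − ρ)) = (1 + ρ)/2, that is 0.65, 0.75 and 0.85 at ρ = 0.3, 0.5 and 0.7.

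**Coverage for MVPA.** 357 − 230 = 127 girls (35.6%) have no valid baseline record: 179 − 114 = 65 control and 178 − 116 = 62 intervention. The Discussion attributes unusable data for 50 participants to device malfunction.

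**The case against.** The strongest reply is that d is only a standardised summary. The tests come from mixed models, and the planned mean difference could itself be a group-by-time contrast from such a model. This largely stands, and it limits the point in four ways.

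- A reader might infer that the trial's tests are biased or lose power. The rule does not govern the tests, so no power loss follows from it.
- A reader might infer that d departs from a baseline-adjusted model result that the article already plans. The article states no such adjustment. Baseline adjustment is the remedy proposed here, not something the plan contradicts.
- A reader might infer that 127 girls necessarily drop out, or that intention-to-treat is breached. The wording does not say that d is built from individual pairs. Baseline assessment also preceded randomisation, and the missing records are almost equal between arms (65 and 62). If pairs are used, precision and coverage suffer, but bias in the comparison is not shown.
- A reader might infer that a change score is biased in general, or that muscular fitness as a whole is affected. The change score is unbiased over randomisations; the shift is conditional on the observed gaps. Of the two fitness measures only prone support shows one.

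It is also fair that no gap exceeds 0.20 SD, that none is significant, and that a persistent school-level component would shrink the shift. None of this makes the raw-change numerator the better choice: the gaps are known, the baseline data are in hand, and adjustment is more precise over the range of ρ considered.

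**Conclusion.** The point holds for the reported effect sizes of MVPA, prone support, body fat and SSR. Given the Table 5 gaps, d would shift by roughly 0.05 to 0.12 if an individual-level ρ of 0.3 to 0.7 applied to the whole gap, and by less if school-level differences persist. The direction is against the intervention for MVPA and prone support and in its favour for body fat and SSR. Baseline adjustment would cut the variance to 0.65 to 0.85 of that of the change score over the same range. BMI is practically unaffected. The sizes rest on an assumed ρ and on equal variances at both visits; the exclusion of 127 girls from the MVPA effect size rests on d being computed from individual pairs. This is a modest improvement to secondary-outcome reporting that is worth making; it does not put the primary analysis in doubt.

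**What to change.** State that the numerator of d is the between-group difference at 12 and at 24 months, estimated from the mixed model with the baseline value of that outcome adjusted for, and divide it by the SD already named. Preferably adjust through a constrained common baseline mean, so that girls with a follow-up measurement but no valid baseline record stay in. A plain baseline covariate would drop those girls unless the baseline is imputed. Apply the rule to every outcome for which d is reported.

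The cost is one sentence of analysis wording and a little programming, with no new data. The downside is slightly less direct comparability with studies that report d from raw change.
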